##### Additional analyses

Subgroup analysis: Subgroup analysis via an interaction by gender, age (18–24, 25–44, and 45–60 years), and BMI (<23 and ≥23 kg/m^2^) will be used to analyze the primary and secondary outcomes among subgroups.Safety analysis: General safety evaluations will be based on the incidence and type of adverse events. Safety variables will be tabulated and presented for all participants in the safety set. Adverse events will be coded using the World SIVA adverse sedation event reporting tool. The number (%) of participants with any adverse events will be summarized.

#### Methods to handle protocol nonadherence and statistical methods to handle missing data

Statistical analysis will be conducted on an intention-to-treat basis. The outcomes will be analyzed as randomized, regardless of protocol adherence. All variables will be screened for frequency and type of missingness. Multiple imputation will be used if missingness is >5% in any variable. In the case of missing data and imputation, complete case analysis will be performed as a sensitivity analysis.

#### Dissemination plans

The study results will be disseminated through articles published in peer-reviewed journals.

#### Additional consent provisions for the collection and use of participant data and biological specimens

No ancillary study is planned, and no plans are in place to collect additional participant data or biological specimens outside of what is mentioned in this protocol.

#### Adverse event reporting and harm

Remimazolam tosylate, a new rapidly metabolizing benzodiazepine, may cause some minor adverse effects but is generally well tolerated. We will evaluate any harm from the intervention. There is a commentary section in study-specific CRFs where researchers can report allocation violations or any unexpected side effects from the allocated intervention. We will collect all expected and unexpected drug-related adverse events nonsystematically and will report all harm in trial publications.

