Treatment of respiratory-related adverse events: When SpO_2_ is <95%, the participant will be lifted to the mandible. If SpO_2_ is <90%, the oxygen flow of the nasal catheter will be increased to 6L/min. If SpO_2_ is still <90%, the procedure will be stopped, the upper gastrointestinal endoscope will be pulled out, and positive pressure ventilation will be performed using a mask. If SpO_2_ cannot be corrected, laryngeal mask airway or tracheal intubation will be performed to control breathing

**Table 4 Tab4:** Adverse events of anesthesia and sedation

Step 1: Was there one or more adverse events associated with this sedation encounter?				
No, this form is now complete.	Yes, fill out remainder of form below.			
Step 2: Please DESCRIBE the adverse events(s). Check all that apply.				
Minimal risk descriptors	Minor risk descriptors		Sentinel risk descriptors	
Vomiting/Retching	Oxygen desaturation (75–90%) for <60s		Oxygen desaturation, severe (<75% at any time) or prolonged (<90% for >60s)	Other, specify below
Subclinical respiratory depression^a^	Apnea, not prolonged		Apnea, prolonged (>60 s)	
Muscle rigidity, myoclonus	Airway obstruction		Cardiovascular collapse/shock^g^	
Hypersalivation	Failed sedation^e^		Cardiac arrest/absent pulse	
Paradoxical response^b^	Allergic reaction without anaphylaxis			
Recovery agitation^c^	Bradycardia^f^			
Prolonged recovery^d^	Tachycardia^f^			
	Hypotension^f^			
	Hypertension^f^			
	Seizure			
Step 3: Please note the INTERVENTIONS performed to treat the adverse events(s). Check all that apply.				
Minimal risk	Minor risk	Moderate risk	Sentinel intervention	
No intervention performed	Airway repositioning	Bag valve mask-assisted ventilation	Chest compressions	Other, specify below
Administration of:	Tactile stimulation	Laryngeal mask airway	Tracheal intubation	
Additional sedative(s)	or the administration of:	Oral/nasal airway	or the administration of:	
Antiemetic	Supplemental oxygen, new or increased	Continuous positive airway pressure (CPAP)	Neuromuscular block	
Antihistamine	Antisialogogue	or the administration of:	Pressor/epinephrine	
		Reversal agents	Atropine to treat bradycardia	
		Rapid i.v. fluids		
		Anticonvulsant i.v.		
Step 4: Please note the OUTCOME of the adverse events(s). Check all that apply.				
Minimal risk outcome	Moderate risk outcome		Sentinel outcome	
No adverse outcome	Unplanned hospitalization or escalation of care^h^		Death	Other, specify below
			Permanent neurological deficit	

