			Pulmonary aspiration syndrome^i^	
Step 5: Assign a SEVERITY rating to the adverse event(s) associated with this sedation encounter.				
If there are any options checked in the Sentinel columns above, then this is a Sentinel^j^ adverse event.				
If the most serious option(s) checked above are Moderate risk, then this is a Moderate^k^ risk adverse event.				
If the most serious option(s) checked above are Minor risk, then this is a Minor^l^ risk adverse event.				
If the most serious option(s) checked above are Minimal risk, then this is a Minimal^m^ risk adverse event.				

Additional details (including “other” entries):

Footnotes:

^a^“Subclinical respiratory depression” is defined as capnographic abnormalities suggesting respiratory depression that do not manifest clinically

^b^“Paradoxical response” is defined as unanticipated restlessness or agitation in response to sedatives

^c^“Recovery agitation” is defined as abnormal patient affect or behaviors during the recovery phase that can include crying, agitation, delirium, dysphoria, hallucinations, or nightmares

^d^“Prolonged recovery” is defined as failure to return to baseline clinical status within 2 h

^e^“Failed sedation” is defined as inability to attain suitable conditions to humanely perform the procedure

^f^Alteration in vital signs (bradycardia, tachycardia, hypotension, hypertension) is defined as a change of >25% from baseline.

^g^“Cardiovascular collapse/shock” is defined as clinical evidence of inadequate perfusion

^h^Examples of “escalation of care” include transfer from ward to intensive care, and prolonged hospitalization

^i^“Pulmonary aspiration syndrome” is defined as known or suspected inhalation of foreign material such as gastric contents into the respiratory tract associated with new or worsening respiratory signs

^j^“Sentinel” adverse events are those critical enough to represent real or serious imminent risk of serious and major patient injury. Once recognized, they warrant immediate and aggressive rescue interventions. Once clinically concluded, they warrant immediate reporting within sedation care systems, and the highest level of peer scrutiny for continuous quality improvement

^k^“Moderate” adverse events are those that, while not sentinel, are serious enough to quickly endanger the patient if not promptly managed. Once clinically concluded, they warrant timely reporting within sedation care systems, and periodic peer scrutiny for continuous quality improvement

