#### Outcome measures

Primary outcome measures

The primary outcome is the success rate of remimazolam tosylate for sedation for diagnosis and treatment during upper gastrointestinal endoscopy. Success is defined by a composite measure (all three conditions must be met) of the following:Completion of the procedure of upper gastrointestinal endoscopy.No requirement for rescue sedative medication.After administering the initial dose of the trial drug, additional administration is ≤2 times within any 5-min period.

Secondary outcome measures

The secondary outcomes are as follows:The induction time of sedation: defined as the time interval from the initial administration of the trial drug to the first MOAA/S score of ≤2.The time of full alertness: defined as the time from the discontinuation of sedative medication to full alertness (the first of three consecutive MOAA/S scores of 5).The incidence of drug injection pain.Digestive endoscopist and participant satisfaction, measured on a scale from 1 to 10. Endoscopists and participants will score their satisfaction with the scale, with 1–3 (dissatisfied), 4–6 (satisfied), or 7–10 (very satisfied), after upper gastrointestinal endoscopy.The time of discharge: defined as the time interval from the termination of the administration of the trial drug to meeting the discharge criteria (modified postanesthesia discharge scoring system score of ≥9, with two points in the vital sign item).The incidence of hypoxia during sedation: defined as 75% ≤ SpO_2_ < 90% for <60 s.All adverse events occurring during the procedure were recorded using tools proposed by the World Society of Intravenous Anesthesia (SIVA)’s International Sedation Task Force [19].

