#### Allocation masking

This study follows a single-blinded method. All participants are blinded to the assignment of the trial (the injection site will be shielded) and will be randomly assigned to any of the three groups.

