##### Statistical analysis plan

All statistical analyses in this experiment will be programmed and calculated using the SAS analytics software version 9.4. In this study, the noninferiority one-sided test used for the main efficacy outcome is that a *P*-value of ≤0.0125 will be considered statistically significant. All other tests will be two-sided tests, with a *P*-value of ≤0.05 considered statistically significant, and the confidence interval will be set at 95%.

Measurement of basic data in different treatment groups will be statistically expressed as mean ± standard deviation or median (interquartile range [IQR]).

The *χ*^2^ test will be used for the success rate of sedation, incidence of injection pain, hypoxia, and adverse events. The analysis of variance will be used to induce time of sedation, full alertness, and discharge. The rank sum test will be used for calculating the satisfaction of endoscopists and participants.

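### The harm section's nonsystematic collection of drug-related adverse events contradicts the structured all-events form used elsewhere, and the stated recording window leaves out that form's own recovery items

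*Protocol article*

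**What the plan says.** The protocol article describes adverse-event collection in several places.

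- **Outcome measures:** "All adverse events occurring during the procedure were recorded using tools proposed by the World Society of Intravenous Anesthesia". The scope is all events, the method is a structured tool, and the window is the procedure.
- **Procedure of the trial, Table 4:** the form is printed in full and opens with "Step 1: Was there one or more adverse events associated with this sedation encounter". It then asks for events, interventions, outcome and severity. It has no drug-causality filter. Its items include recovery agitation, which footnote c places in the recovery phase, and prolonged recovery, which "is defined as failure to return to baseline clinical status within 2 h".
- **Participant timeline (text under Fig. 1):** adverse-event assessment is again tied to the procedure.
- **Additional analyses:** "Adverse events will be coded using the World SIVA adverse sedation event reporting tool". The summary is the number and percentage of participants with any event.
- **Adverse event reporting and harm:** "There is a commentary section in study-specific CRFs where researchers can report allocation violations or any unexpected side effects from the allocated intervention". The section then says: "We will collect all expected and unexpected drug-related adverse events nonsystematically and will report all harm in trial publications".

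Two other statements bear on the consequences. Allocation masking says: "This study follows a single-blinded method. All participants are blinded to the assignment of the trial (the injection site will be shielded". The statistical analysis plan section says the chi-square "test will be used for the success rate of sedation, incidence of injection pain, hypoxia, and adverse events", two-sided at 0.05.

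**The concern.** Site staff cannot follow both accounts. Under one, every sedation encounter gets the same form and every event counts. Under the other, events are noted as they come up and only if someone thinks the drug caused them.

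The second account matters because safety is a stated aim and adverse-event incidence is compared between arms. No masking of the sedation provider or the event recorder is stated. The article also sets out expectations by arm: its Discussion associates propofol with haemodynamic suppression and remimazolam with less hypotension and injection pain. Someone who knows the allocation and shares those expectations would decide whether an event is noted and whether it counts as drug-related. No data-monitoring committee or conduct audit is planned, and data-management checks cannot recover events that were never written down.

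The window is a separate problem. Read literally, a record that closes with the procedure cannot hold two items that the form itself lists.

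**Working it through.** **Step 1. Setting the statements side by side**

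| | Outcome measures, Table 4, Additional analyses | Adverse event reporting and harm |
|---|---|---|
| Scope | All events, no causality filter | Drug-related events, expected and unexpected |
| Method | Structured form, yes/no opening item | Nonsystematic, with a free-text CRF section |
| Window | During the procedure (Outcome measures) | Not stated |

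The harm section names expected events. For a sedative these are events such as desaturation, apnoea, hypotension and bradycardia, which are the items on the form. The two accounts therefore overlap and do not simply cover different events.

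**Step 2. Window against form content**

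Prolonged recovery can be judged only against a 2-hour limit, and recovery agitation is defined by the recovery phase. Both fall after the procedure. Observation does continue: Table 2 monitors until full alertness, and time to meeting discharge criteria is a secondary outcome. The opportunity to record these events exists, but the stated window does not use it.

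**Step 3. Which events are exposed**

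- *Less exposed:* desaturation has SpO2 and duration thresholds, and bradycardia, tachycardia, hypotension and hypertension are changes of more than 25% from baseline. SpO2, heart rate and blood pressure follow one Table 2 schedule in every arm.
- *More exposed:* paradoxical response, recovery agitation, failed sedation, events after the procedure, and any decision that an event is drug-related.

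**Step 4. Illustration of size**

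The plan gives no adverse-event rate or recording probability, so there is no figure to reproduce. Inputs:

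- n = 600 per arm (Sample size section) and a two-sided level of 0.05 (statistical analysis plan section);
- true risk p, equal in two arms: assumed, 5% to 30%;
- one arm records all its events and the other a fraction c: assumed, 90% or 80%;
- a comparison of two arms.

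With p1 = p, p2 = c·p, d = p1 − p2 and p̄ = (p1 + p2)/2:

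- SE0 = √(2·p̄·(1 − p̄)/n)
- SE1 = √([p1(1 − p1) + p2(1 − p2)]/n)
- P(reject) = Φ((d − 1.96·SE0)/SE1) + Φ((−d − 1.96·SE0)/SE1)

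Example with p = 0.20 and c = 0.80: p1 = 0.20, p2 = 0.16, d = 0.04, p̄ = 0.18. SE0 = √(2 × 0.18 × 0.82/600) = 0.0222. SE1 = √((0.16 + 0.1344)/600) = 0.0222. The first term is Φ((0.04 − 0.0435)/0.0222) ≈ 0.438 and the second is negligible, so P(reject) ≈ 0.438.

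| True risk | c = 100% | c = 90% | c = 80% |
|---|---|---|---|
| 5% | 5% | 6.9% | 13.3% |
| 10% | 5% | 9.1% | 22.7% |
| 20% | 5% | 14.3% | 43.8% |
| 30% | 5% | 21.0% | 64.9% |

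If the 10% dropout allowance is used up (600 × 0.9 = 540 per arm), the ranges are 6.7% to 19.4% for c = 90% and 12.4% to 60.3% for c = 80%. When recording is equal, the rate stays at 5%, so any distortion requires recording to differ by arm.

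**The case against.** The strongest reply is that the analysed data already rest on the form. Additional analyses codes events with the World SIVA tool and counts participants with any event, and no sentence says the chi-square comparison draws on the harm section's reports. That stands, and it limits the concern. It does not settle which collection rule sites should follow.

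A second reply is that the harm section may describe a supplement: the form for sedation events and spontaneous reports for the rest. A reader might infer the opposite, that only drug-related events will be collected. The text supports neither reading. It contains no restriction to drug-related events alone, and it also promises to report all harm. But it names expected events, which are the form's own content, and it nowhere describes itself as supplementary.

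A third reply is that the main cardiorespiratory events have fixed thresholds on a common schedule, which leaves little room for discretion. That stands.

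A fourth concerns recovery events. A reader might infer that they will be lost. The form has boxes for them, it refers to the whole sedation encounter, and participants are observed into recovery. The stated window is inconsistent with the form, but this does not show that the events go uncollected.

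Finally, unmasked staff are inferred from the single-blind description and not stated in words. The inference is natural because participants are the only people named as blinded, but it remains an inference.

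**Conclusion.** The contradiction is real: the harm section conflicts with the outcome section, Table 4 and the safety analysis on scope and method, and the procedure-only window conflicts with the form's recovery items. If sites followed the harm section as written, judgement-based and recovery events could be recorded differently by arm. Threshold-based SpO2, heart rate and blood pressure events would be much less affected.

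A reader might infer that the safety comparison is already compromised, or that a spurious advantage for one drug is likely. The documents do not support that. They permit differential recording but do not show it, and the size depends wholly on assumed values. For example, with 600 per arm, a true risk of 20% and 95% versus 70% of events recorded, the observed rates are 19% and 14% (z about 2.3, p about 0.02). The same recording fractions at a true risk of 10% give 9.5% and 7.0% (p about 0.12). A true risk of 20% with 95% versus 85% recorded gives 19% and 17% (p about 0.37). The false-positive ranges of about 7% to 21% and 13% to 65% are illustrations on assumed inputs, and a uniform shortfall across all event types is itself unlikely given the fixed thresholds. The wording should be corrected, but it does not invalidate the design.

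**What to change.** Replace the sentence on nonsystematic collection in Adverse event reporting and harm with one rule. One World SIVA form, including the Step 1 yes/no item, is completed for every dosed participant, from first dose until discharge criteria are met, for all events regardless of attributed cause. The free-text CRF section can stay as an addition to the form.

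State that the between-arm comparison uses all events on the form and that relatedness is reported descriptively. Change the procedure-only wording in Outcome measures and in the text under Fig. 1 to the same window.

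The cost is protocol and CRF wording, plus completing the form through recovery, when participants are already observed. A uniform form removes the discretion over whether to record and the causality filter. The same staff would still complete it, so bias from unmasked recorders is reduced but not removed. No dose or clinical rule changes.

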## Discussion

Our previous study demonstrated that most patients (85.4%) felt uncomfortable during unsedated gastroscopy and 2.1% of the patients reported extreme discomfort. Vomiting/retching was the most common adverse event reported during unsedated gastroscopy. A larger number of gastroscope-intubation attempts and a longer procedure time were needed for unsedated gastroscopy. Therefore, sedative gastroscopy is essential for patients [20]. However, the sedation rate for gastrointestinal endoscopy is much lower in China than in the USA and Europe [21].

Significant developments in endoscopic sedatives have been made in the past decade with participant safety and comfort being the primary focus. However, sedation increases the costs and poses a risk for complications [22].

In the past, propofol and midazolam were the main drugs used for gastrointestinal endoscopic sedation [1]. Propofol is the preferred medication, especially by anesthesiologists. However, propofol use is usually associated with hemodynamic suppression [23]. It is a very negative inotropic drug wherein any decrease in the cardiac output cannot be compensated by an increase in the heart rate. Furthermore, propofol inhibits the sympathetic tone, indicating that cardiac output often drops significantly after a bolus dose. This is most pronounced in patients with impaired cardiac function, especially the elderly and neonates. Propofol induces dose-dependent respiratory depression, whose incidence and duration depend on age, dose, rate of injection, and co-administration of other sedatives/analgesics [24].

Midazolam is the most commonly used sedative drug because of the legal restriction of propofol. Midazolam has a slower onset of action and a relatively longer half-life time (1 h). It is metabolized into active metabolites and interacts with all drugs metabolized through the cytochrome P450 pathway [25]. Furthermore, the creation of active metabolites may lead to a longer and less predictable recovery from sedation [8]. Considering the increasing demand for gastrointestinal endoscopy and disadvantages of existing anesthetics, the development of more effective agents with a more tolerable profile is required urgently.

Remimazolam is a new and rapidly metabolizing benzodiazepine drug [26] produced from a method developed for “soft” drugs to form compounds by fusing known sedative hypnotic drugs with metabolically unstable parts (most commonly esters) to promote predictable and rapid enzyme metabolism, thereby increasing hemodynamic stability and reducing adverse reactions associated with the parent compound [27, 28]. After the resulting structural modification, it undergoes organ-independent metabolism by tissue esterases into an inactive metabolite [29]. Remimazolam is rapidly hydrolyzed to carboxylic acid CNS 7054 [10], and its in vitro affinity for human GABAA receptors is 400 times lower than that of midazolam [14]. Thus, the metabolite is not expected to produce important behavioral effects. Animal studies have confirmed that remimazolam is a potent, rapidly metabolizing hypnotic with a significantly shorter duration of action than that of midazolam. In mice, approximately equihypnotic doses of remimazolam and midazolam produced loss of righting reflexes for durations of several minutes and nearly an hour, respectively [10]. Remimazolam produces modest respiratory and cardiovascular depression at sedating doses, a side effect profile shared with midazolam and other benzodiazepines [26, 30]. Studies have shown that remimazolam has a sedative effect in sheep, and a dose of 0.37–2.21 mg/kg can produce a short-term sedative effect without causing excessive respiratory or cardiovascular depression [26]. Furthermore, comparing the advantages and disadvantages of remimazolam with those of midazolam and propofol in sheep, remimazolam has a rapid offset and greater depth of sedation compared with those of midazolam [30]. In a phase I clinical study, compared with midazolam, remimazolam showed a rapid onset, could be offset, was well tolerated, and had basically stable hemodynamics [14]. Remimazolam had a higher success rate [31], and the waking up time was shorter [32] compared with that of midazolam. Other clinical studies have also reported similar results [33, 34]. Preliminary phase II clinical trials have also shown minimal residual effects of remimazolam in long-term infusions [35]. Studies have shown that remimazolam can effectively replace propofol in gastrointestinal endoscopic sedation without compromising the quality of sedation [36]. In a multicenter, single-blind, randomized, parallel-group phase IIb/III trial, remimazolam was well tolerated as a sedative and hypnotic for general anesthesia and was not inferior to propofol [37]. Based on the abovementioned advantages, remimazolam is very suitable for anesthesia for procedures such as bronchoscopy and gastrointestinal endoscopy. Studies have shown that in bronchoscopy, remimazolam has an effective sedative effect, a medication with rapid onset and recovery compared with midazolam [38]. Phase I–III studies of gastrointestinal endoscopy have also shown that remimazolam presented sufficient sedation, rapid recovery, and rapid recovery of the nerve function compared with midazolam [13, 39–41]. Compared with propofol, remimazolam use has less injection pain and hypotension, characterized by a strong candidate replacement drug for propofol and midazolam in gastrointestinal endoscopy anesthesia [37].

Remimazolam tosylate is a new short-acting GABAA receptor agonist developed by HengRui Medicine Co., Ltd., China. It has been approved by the National Medical Products Administration as a new anesthetic and sedative in 2019 [42]. Remimazolam tosylate has been investigated as a novel ultra-short-acting benzodiazepine in a phase III clinical trial for procedural sedation in China [43]. The study showed that a single dose of remimazolam tosylate (5.0 mg), followed by top-up doses as necessary, was noninferior to propofol in providing adequate sedation, with a very high success rate for patients undergoing upper gastrointestinal endoscopy. The initial low dose of 5.0 mg for remimazolam tosylate may not sufficiently induce rapid sedation. Thus, investigations on the optimized initial loading dose remain to be warranted.

Based on previous studies [44–46], we administered fixed doses of sufentanil. Fixed-dose administration is convenient and more in line with clinical practice.

Based on the existing data, remimazolam tosylate is promising to be used as a sedative agent for outpatient procedural sedation where predictable and rapid recovery is highly desirable. However, no clear standard has been established for the current dosage. Excessive use can cause respiratory depression, a fatal condition when involving personnel without professional training in airway management. Furthermore, if the dosage is insufficient, the participant cannot achieve ideal sedation. Further studies on human subjects are needed to completely characterize its action, which will define the optimal dosing regimens and to determine whether metabolite accumulation with prolonged infusion delays recovery.

